**Data Analysis**

Descriptive statistics: all continuous outcomes and independent variables will be assessed for normality and summarized with mean (SD) and range if normally distributed, or median (interquartile range, IQR) if the distribution is skewed. Categorical variables will be summarized with frequencies and percentage of non-missing values.

Comparisons between the control and intervention groups: initial statistical analyses will consist of univariate tests comparing all outcomes and independent variables between the control and intervention groups. Normally distributed continuous variables will be compared with two-sample t tests, and skewed continuous variables with Wilcoxon rank sums tests. Categorical variables will be compared between groups with chi-square tests, or Fisher’s exact tests if 1 or more expected cell frequencies is less than 5. For the mYPAS, comparisons between groups will be made at each of the 3 time periods. Differences within groups between the mYPAS scores at the 3 time periods will be determined with one-way repeated measures analysis of variance (ANOVA) or Friedman’s ANOVA, depending on the distribution of the data.

If randomization does not result in the groups being balanced for any of the independent variables, particularly the SSP-2, multivariable statistical analyses will be conducted to control for the variables that are different between the groups. For mYPAS scores and scores on the Patient Experience Survey, either multiple linear regression or generalized linear models will be used, depending on the distribution of the outcomes. For the CIBA, with 3 levels of responses, ordinal logistic regression will be used to compare the response levels between groups, controlling for any confounding variables.

An intention-to-treat analysis, in which participants will be analyzed based on the group they were initially allocated to, will be employed. Degree of crossover, in which families request placement in the opposite group from allocation, will be reviewed. Should there be significant crossover of participants, then data will also be analyzed according to the groups in which patients were managed.

Sample size estimation: in previous randomized clinical trials using the mYPAS, investigators considered a difference between groups of ≥15 points to be clinically meaningful.10-12 Standard deviations reported in 1 of the studies ranged from 4.2-18.1.12 Using alpha = 0.05, power = 0.80, and pooled SD = 18.1, 23 patients would be required in each group to detect a difference of 15 points in mean mYPAS scores. Allowing for a 10% drop out rate, 26 patients in each group or 52 patients in total would be required.

Departments involved/supporting: Department of Pediatric Anesthesiology, Child Life and Perioperative Services

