After registration and informed consent, the patient will be placed in either a standard preoperative room (control) or the dedicated sensory rooms (intervention) in the preoperative surgery area based on prior randomization. For the standard practice environment group, the patient will be reserved a standard room in the preoperative area of main campus. This room will not include any additional sensory equipment as described below. The child will be allowed to use any comfort items the family brought with them or offered a hospital iPad, as is current practice for all outpatient surgery patients. For the sensory adaptive environment group, one of the three dedicated adaptive sensory rooms in the preoperative area of main campus will be set up by nursing and child life staff in accordance with the patient’s coping plan and individual needs regarding sound, light, activity level, and other stimuli. The equipment may include a portable popcorn tube with fiberoptic cart, handheld marble panel, color changing floor tiles, other sensory friendly objects, and individual sensory toys. This room will be set up prior to the patient’s arrival the day of surgery and reserved for their use. If a family requests a change from the study randomized perioperative environment, their request will be granted as to not cause potential anxiety or adverse harm to the patient.

The patient’s behaviors will be recorded by a research personnel at three time points during the preoperative waiting time. These time points will be at registration in the surgery lobby, preoperative nurse intake in the individual room, and immediately prior to transition to operating room. The validated modified Yale Preoperative Anxiety Scale (mYPAS) will be utilized to assess anxiety and behaviors. The mYPAS is the most widely used tool for assessing preoperative anxiety in children. It has high reliability, concurrent validity, and construct validity in children aged 2-12 years.6 The mYPAS consists of 5 items; 4 of the items (Activity, Emotional Expressivity, State of Apparent Arousal, and Use of Parent) are rated on scales of 1-4, and 1 item (Vocalizations) is rated on a scale of 1-6. The total score is determined by dividing each item rating by its highest possible rating, summing the results, dividing by 5, and then multiplying by 100. Total scores can range from 23.33 to 100, with higher scores representing greater anxiety. The total score on the mYPAS will be the primary outcome for the study.

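### The mYPAS primary outcome has no named time point and is compared between arms at three ratings, one of them before room placement, although the sample size assumes a single comparison

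*Protocol*

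**What the plan says.** The Methodology section of the protocol states: "The total score on the mYPAS will be the primary outcome for the study". It names no time point, change score or summary over time. Behaviour is rated three times: "at registration in the surgery lobby, preoperative nurse intake in the individual room, and immediately prior to transition to operating room".

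The same section puts the room after the first of these: "After registration and informed consent, the patient will be placed in either a standard preoperative room (control) or the dedicated sensory rooms (intervention". The lobby rating is therefore pre-placement and the other two are post-placement.

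The Data Analysis section fixes the between-arm analysis: "For the mYPAS, comparisons between groups will be made at each of the 3 time periods". The tests are generic: "Normally distributed continuous variables will be compared with two-sample t tests, and skewed continuous variables with Wilcoxon rank sums tests". The same paragraph adds repeated-measures or Friedman tests of change over the three ratings within each group. It does not designate a primary rating, an order of testing or a multiplicity adjustment.

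The sample size paragraph rests on one difference. Its aim is "to detect a difference of 15 points in mean mYPAS scores", and its inputs and result are these: "Using alpha = 0.05, power = 0.80, and pooled SD = 18.1, 23 patients would be required in each group". It does not say at which rating that difference is expected.

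**The concern.** Read together, these sections define three between-arm tests of the primary outcome and size the trial for one. A mixed result, such as a difference at nurse intake but none just before the operating room, has no prespecified reading. The rating that decides whether the trial is positive could then be chosen after the data are seen.

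The lobby rating stands on equal terms with the other two, although it precedes the intervention. It is also absent from the listed independent variables, so the plan to adjust for unbalanced independent variables does not clearly reach it. A natural baseline measure is treated as an outcome.

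At stake are the error rate of the primary claim and a clear definition of a positive trial.

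**Working it through.** **1. The protocol's own figure.** Inputs from the sample size paragraph: difference 15, SD 18.1, alpha 0.05, power 0.80. Sidedness is not stated.

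n per group = 2 × (1.960 + 0.842)² × 18.1² / 15² = 2 × 7.85 × 327.61 / 225 ≈ 22.9, so 23. With 10% dropout, 23 / 0.9 = 25.6, so 26 per group and 52 in total.

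Both stated figures are reproduced for one two-sided test by the normal approximation. The noncentral t gives 23.9, so 24; a one-sided test gives 19 and does not match. The figure is right for a single comparison.

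**2. Number of tests.** There are three between-arm tests, of which two follow room placement.

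**3. False-positive rate if each test is run at two-sided 0.05.** The 0.05 is carried over from the sample size paragraph. With independent tests:

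- two tests: 1 − 0.95² = 9.75%
- three tests: 1 − 0.95³ = 14.3%

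Repeated ratings of one child are correlated, which lowers these rates. The protocol gives no correlation, so a range is assumed. The table gives the chance of at least one significant result when there is no difference at any rating. It comes from simulating equally correlated normal test statistics (2,000,000 draws).

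| Correlation | Two post-placement ratings | All three ratings |
|---|---|---|
| 0 | 9.8% | 14.3% |
| 0.3 | 9.5% | 13.6% |
| 0.5 | 9.1% | 12.6% |
| 0.7 | 8.3% | 10.9% |
| 0.8 | 7.8% | 9.8% |
| 0.9 | 7.1% | 8.4% |

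Against the nominal 5%, this is about 1.4 to 1.95 times for the two ratings that can show an effect of the room (7.1/5 to 9.75/5). For all three it is about 1.7 to 2.9 times (8.4/5 to 14.3/5).

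**4. What the remedies cost in patients.** Naming one post-placement rating as primary leaves alpha at 0.05 and n at 23, or 26 with dropout. For comparison, noncentral-t power for 15 points and SD 18.1 under a Bonferroni split would be:

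| Evaluable per arm | One test (0.05) | Two tests (0.025) | Three tests (0.0167) |
|---|---|---|---|
| 23 (calculated minimum) | 78% | 69% | 63% |
| 27 (30 less 10%) | 85% | 77% | 72% |
| 30 (all sixty recruited) | 88% | 82% | 77% |

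**The case against.** The strongest reply is that multiplicity rules are commonly left to a statistical analysis plan, which may exist and is not shown. That would answer mere silence. Here the protocol states an analysis that does not match its own sample size basis, so a later plan would have to override the text. The missing primary time point is the protocol's own defect.

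Several stronger readings are tempting, and the documents do not support them:

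- **The error rate is doubled or more.** This requires counting the registration test as a chance of success, although it cannot show an effect of the room, and a correlation of about 0.8 or lower. For the two relevant ratings, double is a ceiling that is not reached.
- **The protocol tests each rating at 0.05.** The Data Analysis section sets no level for these tests. The 0.05 is inferred from the sample size paragraph and the absence of any adjustment.
- **The trial is too small.** The fall from 78% to 69% or 63% applies to the calculated minimum of 23 per arm. Planned recruitment is sixty, and with 30 evaluable per arm a two-test split keeps 82%. The protocol proposes no such split.
- **A registration difference can only be chance.** Allocation is made beforehand, the sensory room is set up before arrival, and the protocol does not say that the rater is unaware of allocation at registration. Expectation could also contribute. What stands is that the room itself cannot be the cause.
- **The within-arm tests will serve as evidence of effect.** The protocol lists them beside direct between-arm tests and makes no such claim. The risk lies in later reporting.
- **The last rating must be primary.** Nothing in the protocol settles this. Preoperative medication is recorded, but its timing relative to the ratings is not stated.

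**Conclusion.** The point holds. The primary outcome has no time point, the stated between-arm analysis covers three ratings without hierarchy or adjustment, and the sample size is for one comparison at 0.05. The first rating precedes placement and cannot show an effect of the room.

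The inflation is moderate: about 7-10% over the two post-placement ratings, or about 8-14% if registration also counts. Both ranges assume that 0.05 is applied to each test and that the between-time correlation lies between 0.9 and 0. The undefined primary comparison matters more than the exact rate, because it leaves open what counts as a positive trial. The calculated 23 per group, 26 with dropout, stands for a single test.

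**What to change.** Before data are examined, amend the Data Analysis section as follows:

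- Name one post-placement between-arm comparison of the mYPAS total score as primary, at two-sided 0.05, and justify the choice. The rating immediately before transition to the operating room is one option; nurse intake is the other.
- Make the other post-placement rating secondary.
- Drop the between-arm outcome test at registration. Use that score as a prespecified baseline covariate, whether or not the arms look balanced on it. Linear regression, already foreseen for mYPAS, can carry it. State whether rater and family know the allocation at that rating, since this affects how clean the baseline is.
- Report within-arm changes descriptively, not as evidence of effect.
- Name the same rating in the sample size paragraph.

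This costs about one paragraph and no additional patients. The small downside is that the other rating can no longer be claimed as a primary success.

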The second questionnaire is the Short Sensory Profile 2 (SSP-2), which assesses the patient’s sensory processing abilities. The SSP-2 score will be used as a surrogate for the severity of sensory sensitivity in the study patient. The SSP-2 consists of 34 behavioral items measured on 5-point Likert scales from 1 = almost never to 5 = almost always. Items are divided into 4 quadrants for scoring, Seeking (7 items), Avoiding (9 items), Sensitivity (10 items), and Registration (8 items) based on Dunn’s Sensory Processing Framework.7 Two subscale scores, Sensory Processing and Behavioral Responses Associated with Sensory Processing, as well as total scores are also determined. Raw scores are compared to a normal curve and Sensory Profile 2 Classification System developed from a normative sample. Scores >2 standard deviations (SD) below the mean are classified as “much less than others”, those between 1 and 2 SD below the mean are “less than others”, scores between 1 and 2 SD above the mean are “more than others”, and >2 SD above the mean are “much more than others”.8,9 The SSP-2 will be used as an independent variable to compare baseline responses to sensory stimuli between the control and intervention groups. If the groups differ, the SSP-2 scores will be included as a covariate in statistical analyses.

In addition to the SSP-2, the following independent variables will be extracted from the medical record: patient demographics (sex, age, weight), ASA score designated by anesthesiologist, diagnosis and health history, procedure, home medications, preoperative medications including dose and route, intraoperative medications, event times and durations (including preoperative wait time, transport to OR time, induction to anesthesia ready, case length, & recovery time), and first recovery room pain score (documented by PACU RN via FLACC score).

All data will be identified by a code number and will be transferred to a password-protected database for storage and analysis by the research investigator or assistant. All paper documentation will be secured in a locked cabinet until the conclusion of the study, at which time it will be properly disposed.

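### Free improvement: the between-arm mYPAS comparisons leave out each child's pre-room registration score, which is already collected and could be used as a covariate to gain precision

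*Protocol*

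**What the plan says.** The Methodology section states "The total score on the mYPAS will be the primary outcome for the study". On timing it says "These time points will be at registration in the surgery lobby, preoperative nurse intake in the individual room", with a third rating just before the child leaves for the operating room. Placement comes after the first rating: "After registration and informed consent, the patient will be placed in either a standard preoperative room (control) or the dedicated sensory rooms (intervention", so the lobby score precedes exposure to either room.

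The Data Analysis section says that "initial statistical analyses will consist of univariate tests comparing all outcomes and independent variables between the control and intervention groups", by two-sample t or Wilcoxon rank sum tests for continuous variables, and adds "For the mYPAS, comparisons between groups will be made at each of the 3 time periods". A child's own scores are linked over time only in a repeated-measures or Friedman analysis within each arm, which does not compare the arms.

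Regression enters only if the arms turn out unbalanced on the independent variables, in which case "multivariable statistical analyses will be conducted to control for the variables that are different between the groups". The Methodology section defines these as the SSP-2 and then says "the following independent variables will be extracted from the medical record: patient demographics (sex, age, weight), ASA score designated by anesthesiologist", followed by diagnosis, procedure, medications, event times and the first recovery pain score. The Data collection section repeats the medical-record list. mYPAS is in neither place.

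**The concern.** The registration rating measures the primary outcome on the same child, on the same scale, before the room can have had any effect. Two consequences follow from leaving it out of the between-arm comparison.

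First, variation between children that was already present at registration stays in the error term of the later comparisons. Intervals are wider than they need to be.

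Second, with about 27 evaluable children per arm, the arms will often differ by several points at registration by chance. A fraction of that gap, equal on average to the correlation between registration and later scores, passes into the unadjusted later difference. As written, the imbalance rule does not respond to it, because mYPAS is classed as an outcome.

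Testing registration as one of three outcome comparisons also adds a test that cannot show a room effect.

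**Working it through.** **Inputs.** From the sample size paragraph: difference 15 points, SD 18.1 (top of the cited 4.2–18.1 range), alpha 0.05, power 0.80, dropout 10%. From Methodology: 60 children, 1:1. Evaluable per arm: 30 × 0.9 = 27. Assumed, because the documents do not give them: the correlation r between registration and a later mYPAS (0.3, 0.5, 0.7, with 0 as the limit), and the same SD at registration as later.

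**1. The plan's own figure.** n = 2 × (1.960 + 0.842)² × 18.1² / 15² = 22.9, so 23 per arm; 23 / 0.9 = 25.6, so 26 per arm and 52 in total. Both reproduce with a two-sided alpha (one-sided would give 19). The calculation is for an unadjusted two-sample comparison.

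**2. Unadjusted comparison at 27 per arm.** SE = 18.1 × √(2/27) = 4.93. The 95% CI half-width is 2.007 × 4.93 = 9.9 points. Noncentral-t power for 15 points (52 df) is 84.8%.

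**3. With registration mYPAS as covariate.** Residual SD = 18.1 × √(1 − r²), with 51 df.

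| r | Residual SD | Power | CI half-width |
|---|---|---|---|
| unadjusted | 18.1 | 84.8% | 9.9 |
| 0.3 | 17.3 | 87.9% | 9.4 |
| 0.5 | 15.7 | 93.2% | 8.6 |
| 0.7 | 12.9 | 98.7% | 7.1 |

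This formula ignores the small cost of estimating the slope. Simulation (20,000 trials per setting) at 30 per arm gives 88% unadjusted against 90%, 95% and 99% adjusted. At 23 per arm and r = 0, adjustment costs about one point of power (78.5% against 77.5%).

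**4. Type I error over all randomizations.** In the same simulations it is about 5% for both methods.

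**5. A chance gap at registration.** Its SE is also 4.93. P(gap of at least 5 points in either direction) = 2 × P(Z > 5/4.93) = 31%; about 15% have the sensory arm at least 5 points more anxious. Within those trials the mean gap is 4.93 × φ(1.015) / P(Z > 1.015) = 7.6 points. The unadjusted estimate of a true 15-point benefit then averages 15 − 7.6r = 12.7, 11.2 or 9.7 points. In the mirror-image trials it averages 15 + 7.6r = 17.3, 18.8 or 20.3. The two cancel over randomizations. In any one trial, only the covariate removes the shift.

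**6. Sensitivity to the SD.** At SD 14 the SE is 14 × √(2/27) = 3.81, a gap of at least 5 points arises in 19% of trials, and unadjusted power is already 97%. At SD 12 the figures are 13% and 99.5%. There is then little power to gain. The proportional narrowing of the interval, √(1 − r²), does not depend on the SD.

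**The case against.** The strongest reply is that nothing here is invalid. Randomisation makes the unadjusted comparison unbiased with correct type I error. The sample size was computed for exactly this test, and 60 are recruited against 52 required. All of that stands, so a reader who inferred that the primary result is biased, or that the trial is underpowered, would go further than the documents allow. Conditional figures can invite that inference. Among trials whose sensory arm starts at least 5 points worse, unadjusted power is roughly 72%, 62% or 49%. With no effect and a gap of at least 5 points either way, false positives are roughly 7%, 9% or 13%. Both describe selected subsets and are offset elsewhere.

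The size of the gain also rests on two unknowns. No correlation is given, and 18.1 is the largest SD cited. This stands, and the ranges above reflect it.

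A third reply is that the protocol does not forbid the adjustment. The univariate tests are called initial, the list of variables need not be exhaustive, and a statistical analysis plan may exist. It would therefore be too strong to say that the score could never enter a model. But the adjustment clause refers back to the independent variables, and even a loose reading would make adjustment depend on an observed difference. The protocol states the test and the trigger, so this is a choice that can be reviewed as written.

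Finally, children are placed according to a prior randomization, so the registration rating may follow allocation. The protocol does not say whether the rater or family knows the allocation by then. The rating still precedes the room, so its use as a covariate holds, provided that knowledge of allocation does not influence it.

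**Conclusion.** The point holds as a free improvement, not as an error. The protocol compares the arms on mYPAS without the pre-room score, treats that score as an outcome, and limits adjustment to a list that omits it. The planned analysis remains valid on average and meets its 80% power.

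What is given up, at SD 18.1 and 27 per arm, is about 3, 8 or 14 points of power for a 15-point difference (87.9, 93.2 or 98.7 less 84.8) and 0.5, 1.3 or 2.8 points of CI half-width, for assumed correlations of 0.3, 0.5 and 0.7. At a correlation near zero nothing is gained and almost nothing is lost. At an SD of about 14 or less the power gain is small. Protection against a chance gap at registration is the other benefit. It matters for how the single trial actually run is interpreted, not for long-run error rates.

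**What to change.** In the Data Analysis section, for each of the two post-room ratings (nurse intake, and just before transition to the operating room), replace the univariate between-arm test with a linear regression of mYPAS on randomised arm with registration mYPAS as a covariate. Fit it always, not only after an observed imbalance, and report the adjusted mean difference with its 95% CI. Report registration mYPAS by arm as a baseline description, without an outcome test.

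Two additions are optional: robust standard errors, in case scores cluster at the 23.33 minimum, and filling a missing registration score with the overall mean so that no child is dropped. Which of the two ratings is primary is a separate question that this change does not settle.

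The cost is one paragraph of wording and one degree of freedom per model. No new data, children or staff are needed. The change should be made before outcome data are examined by arm, so that the adjustment is not chosen in light of the results.

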**Methodology**

At Dayton Children’s, all patients with autism or other developmental delays are called prior to the day of surgery by child life specialists to obtain a coping plan. The coping plan is a document that details the patient’s previous medical experiences and provides information regarding their communication abilities, specific interests, sensory sensitivities, and triggers that make them upset. Additionally, the child life specialists elicit information regarding the best environment for the child and if they have any comfort items. The above information is documented into the EHR for all staff members to see prior to taking care of the patient the day of surgery.

For this study, inclusion criteria will include patients with a formal diagnosis of Autism Spectrum Disorder, Asperger’s Syndrome, or pervasive developmental disorder NOS patients, who are aged three to twelve years old, presenting for outpatient surgery at main campus. Patients will be excluded if a coping plan is not able to be obtained prior to day of surgery, have an American Society of Anesthesiology (ASA) risk score greater than 3, non-English speaking, or refusal of participation by guardian. Those patients that meet the criteria will be consecutively approached via telephone call 24-48 hours prior to procedure by the research team to describe the study and gauge interest in participating until we recruit sixty patients.

The study will recruit a total of sixty patients in two parallel groups randomized to 1:1 allocation: control group (standard practice with no sensory adaptive environment) or intervention group (sensory adaptive environment). Patients will be randomized in varying block sizes using a random number generator to ensure equal numbers in each group. The random allocation, block sizes, and block sequences will be concealed from study personnel and each patient until the time a patient is assigned to a group.

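### The imbalance-triggered adjustment of the primary outcome is open to variables that arise after randomisation, so the adjusted estimate can be biased in either direction

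*Protocol*

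**What the plan says.** The Methodology section makes the mYPAS total the primary outcome: "The total score on the mYPAS will be the primary outcome for the study". It is scored at registration, at nurse intake in the room, and just before the child leaves for the operating room. Children are placed in rooms according to an allocation already made.

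The same section lists the independent variables: the SSP-2 and items taken from the medical record. Beside demographics, ASA score, diagnosis and health history, procedure and home medications, the list contains "preoperative medications including dose and route, intraoperative medications, event times and durations (including preoperative wait time" and four further times or durations, then the first recovery-room pain score. The Data collection section repeats the medical-record items.

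The Data Analysis section first compares every outcome and every independent variable between arms with univariate tests. It then gives the adjustment rule: "If randomization does not result in the groups being balanced for any of the independent variables, particularly the SSP-2", multivariable analyses follow "to control for the variables that are different between the groups". Linear or generalized linear models are named for the mYPAS and the experience survey. Ordinal logistic regression is named for the CIBA, with control for any confounders. No sentence limits the rule to variables fixed before allocation.

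**The concern.** Randomisation protects a comparison only as long as the analysis does not condition on what happened afterwards. A variable that the room can change is part of the room's effect, or a marker of it, and holding it constant changes the question being answered. Premedication matters most here, because the protocol's long-term goal is to offer sensory rooms as an alternative to it. If the room led to fewer children being premedicated, that difference between arms would itself bring premedication into the mYPAS model.

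The rule also lets observed differences choose the covariates after the data are in. The protocol sets no threshold for imbalance and does not say whether the adjusted or the unadjusted result is decisive. Two analysts following the text could report different answers for the primary outcome.

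**Working it through.** **1. The plan's own sample size.** Inputs, from Data Analysis: "Using alpha = 0.05, power = 0.80, and pooled SD = 18.1", and the aim "to detect a difference of 15 points in mean mYPAS scores". Two-sided alpha is assumed, since sidedness is not stated.

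n per group = 2 × [18.1 × (1.960 + 0.842) / 15]² = 22.86, rounded up to 23. With 10% dropout, 23 / 0.90 = 25.6, rounded up to 26, or 52 in total. This reproduces the plan's figures. An exact t test has power 0.785 at 23 per group and reaches 0.80 at 24, a negligible difference. Methodology plans 60 patients; at 30 per group the unadjusted t test has power of about 0.88.

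**2. Count of the listed variables.**

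- Patient traits or facts fixed beforehand (8): SSP-2, sex, age, weight, ASA score, diagnosis and health history, procedure, home medications.
- Arising after randomisation (8): preoperative medications, intraoperative medications, waiting time, transport time, time from induction to readiness, case length, recovery time, first recovery pain score.

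That is 8 of 16. The exact ratio depends on how items are grouped: splitting diagnosis from health history gives 8 of 17, and counting demographics and event times as one entry each gives 4 of 10.

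**3. Position relative to the mYPAS.** Preoperative medication and waiting time can precede the last mYPAS and can be affected by the room, so they are possible mediators. The other six come after the last mYPAS and cannot cause it. They may still be consequences of the child's anxiety, and adjusting for a consequence of the outcome also distorts the arm comparison.

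**4. How often chance alone could trigger the rule.** If imbalance meant p < 0.05 and the tests were independent (both assumptions), the chance that at least one of the eight later variables differs when nothing truly does is 1 - 0.95^8 = 0.34.

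**5. Direction and possible size.** These are illustrations only: 30 per arm, SD 18.1, true total effect -15, 4,000 runs per scenario, one later variable, adjusted for only when it differs between arms at p < 0.05. Mediator shares, correlations, premedication rates and drug effects are all assumed.

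Expected estimate when the variable is always adjusted for:

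- (a) A mediator carrying share s of the effect: -15 × (1 - s), so -11.25 for s = 0.25 and -7.5 for s = 0.50. The arm shift in the mediator is set at 0.8 SD.
- (b) A consequence of anxiety with within-arm correlation r: -15 × (1 - r²), so -13.65, -11.25 and -7.65 for r = 0.3, 0.5 and 0.7.
- (c) Premedication in 60% of controls and 30% of the sensory arm, lowering the mYPAS by d points: -15 - 0.3d, so -18.0 for d = 10 and -19.5 for d = 15.

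Simulated results under the rule:

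| Scenario | Rule triggered | Mean estimate | Power |
|---|---|---|---|
| (a) s = 0.25 | 86% | -11.6 | 0.65 |
| (a) s = 0.50 | 86% | -7.8 | 0.41 |
| (b) r = 0.3 | 17% | -14.4 | 0.86 |
| (b) r = 0.5 | 35% | -12.9 | 0.80 |
| (b) r = 0.7 | 59% | -9.5 | 0.64 |
| (c) d = 10 | 67% | -17.3 | 0.94 |
| (c) d = 15 | 65% | -18.7 | 0.98 |

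The unadjusted estimate stays at about -15, with power about 0.88, in every scenario. The higher power in (c) comes from overstating the total effect and is not a gain.

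**The case against.** The best defence is intent. The rule opens by asking whether randomisation balanced the groups, singles out the SSP-2, and elsewhere speaks of baseline responses and confounding. Baseline covariates were probably meant. That is a fair reading of the purpose, but the protocol's own list says what counts as an independent variable, and an analyst following it would adjust for premedication if the arms differed on it. A statistical analysis plan may name covariates. The fault, however, lies in a rule that the protocol states, not in detail it left for later.

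Second, the unadjusted tests are always run, under intention to treat, and the multivariable model is never called primary. This stands: a reader might infer that the biased model replaces the randomised comparison, and the text does not say so. It does not say the reverse either. Intention to treat fixes which arm a child is counted in; it does not govern covariates.

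Third, a reader might infer that adjustment shrinks the effect towards zero, perhaps by a stated fraction. The documents do not support that. They present premedication as a treatment for anxiety, and if the room reduces its use, adjustment can overstate the effect, as in (c). They give no premedication rate or effect from which to fix a size.

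Fourth, applying the calculation in step 4 to all 16 variables gives 1 - 0.95^16 = 0.56, which a reader might take as the chance of a contaminated analysis. It is not: half of those variables are traits whose adjustment does not import an effect of the room, the 5% threshold is assumed, and items such as procedure, case length and recovery time are plainly related.

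**Conclusion.** The concern holds in this form: read as written, the rule allows the primary outcome to be adjusted for 8 of about 16 listed variables that arise after randomisation. Two of these can be mediators, and six can only be later events or consequences. When one of them triggers the rule, the adjusted estimate can be biased in either direction. This conclusion rests on the wording and on the order of events, not on any simulation. The size of the bias cannot be derived from the protocol; the range from -7.8 to -18.7 around a true -15 shows only what the assumed scenarios produce. The unadjusted comparison remains valid and reportable, so the trial's evidence is not lost. What is missing is a statement of which result decides. The rule should be corrected before outcome data are examined, because a later change of covariates would be hard to defend.

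**What to change.** - In Data Analysis, delete the imbalance-triggered rule. State that no variable arising after room placement will be adjusted for in the between-arm comparisons of the mYPAS, the experience survey or the CIBA. The Methodology sentence that makes the SSP-2 a covariate only if the groups differ should change to match.
- Name a short covariate set in advance, used whatever the observed balance: registration mYPAS (for the in-room mYPAS time points), age and SSP-2 total. Say which analysis is decisive. Registration mYPAS follows allocation but is scored before the room is entered, so it should be described as measured before room exposure.
- The SSP-2 describes a trait, but parents complete it during the procedure, after seeing the room. Either have it completed before room entry or state its timing as a limitation.
- In Methodology and Data collection, relabel medications given on the day, event times and the recovery pain score as secondary or descriptive data.

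The cost is a few sentences and possibly moving one questionnaire earlier. No new data are needed, and the calculation behind "Allowing for a 10% drop out rate, 26 patients in each group or 52 patients in total would be required" is unaffected, as is the planned total of 60.
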